**Objective:**

This full-scale RCT will examine the effectiveness of the Pulmonary Education and Asthma Knowledge Mobile Asthma Action Plan (PEAKmAAP), an interactive mHealth asthma action plan (mAAP) smartphone app, among adolescents compared to enhanced usual care (eUC). The study has 3 aims: (1) examine the effectiveness of PEAKmAAP in reducing asthma morbidity, as measured by the Asthma Control Test (ACT) score, health care use, medication use, and lung function; (2) examine the effectiveness of PEAKmAAP in asthma self-efficacy and medication adherence; and (3) examine the impact of sharing PEAKmAAP-generated data with the primary care provider (PCP) for a subset of enrolled subjects. We hypothesize that the PEAKmAAP groups will experience reduced asthma morbidity compared to the eUC group. Furthermore, we hypothesize that PCP data sharing is expected to enhance PCP prescribing patterns and that more adolescents in the Pulmonary Education and Asthma Knowledge Mobile Asthma Action Plan with data sharing (PEAKmAAP-DS) group will have sustained controlled at follow-up visits compared to PEAKmAAP alone or eUC.

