To address barriers with written or paper-based AAPs, we developed and conducted feasibility testing of a prototype of the Pulmonary Education and Asthma Knowledge Mobile Asthma Action Plan (PEAKmAAP) among 20 adolescents with persistent asthma over an 8-week study period [21,22]. We demonstrated the feasibility of implementing a smartphone-based mobile health (mHealth) intervention for adolescents, and findings suggested that this innovative tool could result in significant improvements in asthma self-efficacy, as well as clinically significant improvements in ACT scores [23]. among at-risk adolescents. Next, we conducted a pilot randomized controlled trial (RCT) test among 34 adolescents over 6 months to compare the use of the PEAKmAAP prototype in paper-based AAPs [24]. Participant satisfaction was high, with 100% of adolescents stating they would recommend PEAKmAAP to a friend. Further, participants with uncontrolled asthma benefited from use of PEAKmAAP, as suggested by clinically important improvements in Asthma Control Test (ACT) scores (defined as a ≥3-point increase in the ACT score) [23] when compared to participants using paper-based AAPs [24]. Herein, we present the protocol of a full scale RCT aimed to examine the effectiveness of PEAKmAAP, a personalized, interactive smartphone app, among adolescents with uncontrolled asthma. We hypothesize that PEAKmAAP participants will experience reduced asthma morbidity compared to the enhanced usual care (eUC) participants and that sharing PEAKmAAP data with primary care providers (PCPs) will be associated with sustained asthma control over the 12-month intervention period.

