Using these models, the primary outcome of the proportion of participants with ACT scores of >19 at 3 months will be analyzed using linear models with a logit link function and contrasts to compare the 2 PEAKmAAP groups combined with the eUC group. Secondary analyses of the proportion of ACT scores of >19 at additional timepoints (6, 9, 12 months) will be assessed with contrasts for the group effect (to measure the average effect across the different timepoints) and the group-by-time interaction effect (to measure the change in effect over time) between groups (PEAKmAAP-DS vs PEAKmAAP; PEAKmAAP groups combined vs eUC). Since the ACT score will be measured at 3, 6, 9, and 12 months (all participants will have baseline scores of ≤19), these correlated repeated measures data will be analyzed with a binomial distribution and a logit link function for modeling with an appropriate correlation structure (eg, compound symmetry or first-order autoregressive). Additionally, minimally important improvements in ACT scores (3-point increase) and CASI (1-point decrease) will be similarly modeled as binary outcomes across timepoints, contrasting eUC versus the 2 PEAKmAAP groups combined or PEAKmAAP versus PEAKmAAP-DS. Other secondary outcomes (health care use, rescue medication use, lung function) will be analyzed using similar models for nonnormal data using appropriate distributions and link functions.

Medication adherence rates at 12 months will be compared using a logistic regression model after adjusting for baseline values as a covariate, contrasting eUC against the 2 PEAKmAAP groups. Mean asthma self-efficacy scores at 3 and 12 months, including the subscales for prevention and management, will be compared among the 3 groups using the analysis of covariance model after adjusting for baseline values as a covariate in the model. The proportion of adolescents who receive step-up therapy will be compared between the 2 PEAKmAAP groups, and the 2 PEAKmAAP groups together will be compared with the eUC across different timepoints using a similar logistic model.

No interim analyses are planned, and thus, there is no planned stopping rule for the study.

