## Discussion

### Summary

Adolescents with asthma are at increased risk for adverse health outcomes related to asthma and are a group traditionally difficult to engage in self-management strategies for chronic illnesses. Smartphone use is prevalent and has been cited as a preferred and convenient method of communication among adolescents. mHealth delivered via smartphones can provide health education, medication tracking and logging, and chronic disease management integration into the daily lives of patients with asthma [49]. The current literature examining the role of mHealth apps for adolescent asthma is limited. Most studies are small pilot trials with a small number of participants or a short study period. We will test PEAKmAAP’s effectiveness among a large cohort of high-risk adolescents with uncontrolled asthma over a 12-month period. Based on the CCM and by virtue of its convenience, ability to provide immediate feedback, and ease of integration into a daily routine, we will examine the PEAKmAAP intervention as a tool to improve asthma self-management, improve medication adherence, and reduce asthma-related morbidity among adolescents at risk for future exacerbations. Our central hypothesis is that the PEAKmAAP and PEAKmAAP-DS groups will have reduced asthma morbidity compared to the eUC group. We further hypothesize that PCP data sharing will facilitate sustained asthma control and that significantly more adolescents in the PEAKmAAP-DS group will have continued asthma control at follow-up visits compared to PEAKmAAP alone and the eUC group. This novel approach has a high impact potential as it may be applicable to other age groups and patients with other chronic medical conditions.

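### The data-sharing hypothesis counts adolescents who stay controlled, but the planned contrasts compare only visit-wise control rates and omit PEAKmAAP-DS versus eUC

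*Protocol article*

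**What the plan says.** The data-sharing hypothesis appears three times in the Protocol article.

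- Abstract, Objective: more adolescents with data sharing "will have sustained controlled at follow-up visits compared to PEAKmAAP alone or eUC".
- Introduction: sharing data with the PCP "will be associated with sustained asthma control over the 12-month intervention period".
- Discussion, Summary: "significantly more adolescents in the PEAKmAAP-DS group will have continued asthma control at follow-up visits compared to PEAKmAAP alone and the eUC group".

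It corresponds to aim 3. The Summary gives the label of central hypothesis to a different statement: "Our central hypothesis is that the PEAKmAAP and PEAKmAAP-DS groups will have reduced asthma morbidity compared to the eUC group".

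Methods, Statistical Analysis, gives the follow-up analysis of ACT >19. For the measurements at 3, 6, 9 and 12 months, "these correlated repeated measures data will be analyzed with a binomial distribution and a logit link function for modeling with an appropriate correlation structure". The proportions at the later visits "will be assessed with contrasts for the group effect (to measure the average effect across the different timepoints") and for "the group-by-time interaction effect (to measure the change in effect over time) between groups (PEAKmAAP-DS vs PEAKmAAP; PEAKmAAP groups combined vs eUC"). The subsection on ACT secondary outcomes says that the repeated ACT is meant to capture improvement that lasts through the study. Nowhere does the article define lasting control for an individual participant.

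**The concern.** Two parts of the hypothesis have no matching analysis.

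First, the Abstract and the Summary count adolescents whose control is sustained or continued. The most natural reading is a count of people who remain at ACT >19. The planned model compares the proportion controlled at each visit, averaged over visits or allowed to change over visits. A 50% rate at every visit is compatible with the same half of the arm being controlled throughout, and equally with a different half each time. The group-by-time term does not separate these cases. It is zero when a benefit is held constant, and a non-significant result does not demonstrate persistence.

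Second, both statements name eUC as a comparator for PEAKmAAP-DS, but eUC is compared only with the two app groups combined.

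The trial could therefore report that data sharing did, or did not, help adolescents stay controlled from contrasts that do not estimate that quantity.

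**Working it through.** **1. The document's own figures.** Sample Size and Power Calculation gives 107 per group for a difference of 15 (read as percentage points) in ACT >19 at 3 months, two-sided 5%, at least 80% power. The eUC rate is not given. At an assumed 20% versus 35% with 2:1 allocation, the two-proportion formula needs 106 in eUC, and 107 gives 80.6% power. The 124 after attrition equals 107 × 1.15 = 123.05, rounded up (107/0.85 would be 125.9). These figures concern the 3-month primary outcome. Only the 107 is used below.

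**2. Hypothesis against analysis.**

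| Element | Hypothesis (Abstract, Summary) | Statistical Analysis |
|---|---|---|
| Quantity | adolescents with sustained or continued control | control rate by visit: average effect and change in effect |
| PEAKmAAP-DS vs PEAKmAAP | yes | yes |
| PEAKmAAP-DS vs eUC | yes | not listed |

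**3. What the comparators estimate.** On the logit scale, let d be the PEAKmAAP-DS effect and a the PEAKmAAP-alone effect, each against eUC. The listed contrasts estimate d − a and, with equal weights, (d + a)/2. Neither tests d = 0. The value follows from the same model, since d = (d + a)/2 + (d − a)/2, so adding the contrast needs no new model.

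**4. What visit rates say about sustained control.** If a proportion p is controlled at each of four visits, the share controlled at all four lies between max(0, 4p − 3) and p. At p = 0.5 that is 0% to 50%. This bound needs no correlation model.

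**5. Size under an assumed model.** Take p = 0.5 at every visit and an exchangeable latent normal with correlation ρ. The share controlled at all k visits is E[Φ((t − √ρ·z)/√(1−ρ))^k], with t = Φ⁻¹(0.5) = 0 and z standard normal.

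| ρ | k = 3 (6, 9, 12 months) | k = 4 (3 to 12 months) |
|---|---|---|
| 0.3 | 0.198 | 0.140 |
| 0.5 | 0.250 | 0.200 |
| 0.8 | 0.346 | 0.314 |

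Two arms at ρ = 0.3 and 0.8 differ by about 15 points (three visits) or 17 points (four visits). Their average effect and interaction are both exactly zero.

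**6. Check by a second route.** For a first-order Markov chain with visit-to-visit correlation r, the share controlled at all four visits is p(p + r(1 − p))³. At p = 0.5 this is 0.5 × 0.6³ = 0.108 for r = 0.2 and 0.5 × 0.9³ = 0.365 for r = 0.8. In 300 simulated trials of these two arms (107 each, GEE logit model), the average contrast rejected in 5.7% and the interaction in 5.0%, both close to the nominal level. A direct test of the share controlled at all visits rejected in 100%.

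**7. Power of a per-participant outcome.** With n = 107 per arm and two-sided 5%, power = Φ[(δ√n − 1.96√(2p̄q̄)) / √(p₁q₁ + p₂q₂)]. For p₁ = 0.15 and δ = 0.15: (1.552 − 1.158)/0.581 = 0.678, giving 75%. For assumed reference rates of 20%, 25% and 30% the power is 69%, 65% and 62%. Reaching 80% would need 121 to 163 per arm over the range 15–30%. For 10 points the power is 45% down to 33%, and for 20 points 93% down to 85%. None of these includes the Holm-Bonferroni adjustment, which would lower them.

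**The case against.** The per-person reading is not forced. No section says that the same adolescent must exceed 19 at every visit. The Introduction reads easily at group level, and even the Summary could mean a higher proportion controlled at the follow-up visits, which is what the model estimates. This stands as a caution: the article does not settle the reading.

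The two contrasts are planned as a pair. A constant benefit gives a zero interaction but also a positive average effect, so together they describe whether a group difference exists and whether it changes. A reader might infer that the plan can say nothing about sustained control. That goes too far, because maintenance at group level can be shown.

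The example in step 5 is extreme. Data sharing would have to change persistence greatly and the control rate at no visit. If correlation is equal in both arms, the two measures agree in direction: at ρ = 0.5 and three visits, all-visit control is 5%, 13%, 25% and 41% for visit rates of 20%, 35%, 50% and 65%. Under that equal-correlation assumption (a 15-point gain at each visit, reference rates 20–50%, ρ from 0.3 to 0.8, 107 per arm), power is roughly 50% to a little over 70% for the all-visits outcome, against about 75–96% for the average effect. This is a good reason not to replace the planned contrast.

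Finally, a condensed article may leave derived definitions to an analysis plan that is not shown. That would answer a complaint about missing detail. Here the article states both the hypothesis and its test, and the two do not match.

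**Conclusion.** The point holds in a limited form. As written, the plan can show whether a group-level difference in control rates is maintained. It does not estimate how many adolescents stay controlled, and it lists no PEAKmAAP-DS versus eUC contrast although the Abstract and the Summary hypothesise one.

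The bound (0% to 50% controlled at all visits when 50% are controlled at each) assumes only the 50% rate. The 15-point gap also rests on assumed correlations and shows what is possible, not what is expected.

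A reader might also infer that the trial's main question is at risk. The documents do not support that. The central hypothesis is reduced morbidity in both app groups against eUC, data sharing is introduced as a further hypothesis, and the 3-month primary analysis is untouched. This is a worthwhile, inexpensive improvement to a secondary analysis.

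**What to change.** 1. Keep the planned average and group-by-time contrasts, and add PEAKmAAP-DS versus eUC to both.
2. Add a secondary per-participant outcome: ACT >19 at each of 6, 9 and 12 months, with a sensitivity version that also requires 3 months. Derive it from the ACT scores within each multiply imputed data set.
3. Compare it for PEAKmAAP-DS versus PEAKmAAP and PEAKmAAP-DS versus eUC by logistic regression with the severity stratum, within the Holm-Bonferroni correction.
4. Base any statement that individual adolescents sustained control on this outcome. Use the planned contrasts for statements about group-level maintenance.
5. Date the definition. Data collection ended in May 2024 and full analysis began in December 2024, so label it as added after data collection if unblinded results have been seen.

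Cost: analysis-plan wording, one extra contrast and one extra model on data already collected. The all-visits outcome is less frequent, depends more on missed visits and has lower power than the average effect, so it should be reported with confidence intervals, and a non-significant result should not be read as absence of an effect.

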### Sample Size and Power Calculation

The sample size was determined to detect a clinically meaningful difference between PEAKmAAP and PEAKmAAP-DS groups combined versus the eUC group for the primary outcome measure, which is the proportion of adolescents with ACT scores of >19 at 3 months. We estimate that the proportion of participants with ACT scores of >19 at 3 months will be approximately 15% higher in the PEAKmAAP and PEAKmAAP-DS groups compared to the eUC group based on pilot work [24,40]. Using a generalized estimating equations (GEE) model for binary longitudinal data, we estimated that a sample size of 107 participants in each group will yield at least 80% power to detect the difference mentioned before. After adjusting for a 15% attrition rate, the final sample size needed will be 124 in each group (372 total). The sample size will also have at least 80% power to detect a change from a baseline of 4 between the eUC group and PEAKmAAP and PEAKmAAP-DS groups combined for the asthma self-efficacy score. The SD of the asthma self-efficacy score was determined to be 7 [21,22]. The sample size determination was performed using the GEESIZE macro in SAS Software and PASS [46-48]. All sample size calculations assumed a 2-sided significance level of 5%.

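### The 80% power for the 3-month primary outcome is derived from a longitudinal GEE calculation, while the primary test is a single 3-month contrast whose power depends on an unstated control rate

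*Protocol article*

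**What the plan says.** The Sample Size and Power Calculation section names the target of the calculation as "the primary outcome measure, which is the proportion of adolescents with ACT scores of >19 at 3 months", with the two app groups combined and compared with eUC. The expected effect is that this proportion "will be approximately 15% higher in the PEAKmAAP and PEAKmAAP-DS groups compared to the eUC group". The method and the size come in one sentence, which begins "Using a generalized estimating equations (GEE) model for binary longitudinal data, we estimated that a sample size of 107 participants in each group will yield". The power claimed for that difference is 80% or more, and the GEESIZE macro and PASS are the software named. The significance level is two-sided 5%. An allowance for 15% attrition brings the size to 124 per group, 372 in total. The section gives no eUC control rate, number of visits or working correlation.

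The Statistical Analysis section treats the primary outcome at a single visit: "the primary outcome of the proportion of participants with ACT scores of >19 at 3 months will be analyzed using linear models with a logit". The comparison is a contrast of the combined app groups with eUC. The later visits are treated separately: "Secondary analyses of the proportion of ACT scores of >19 at additional timepoints (6, 9, 12 months) will be assessed with contrasts". The correlated-data model is introduced for that purpose: "Since the ACT score will be measured at 3, 6, 9, and 12 months (all participants will have baseline scores of ≤19").

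**The concern.** The method named for sizing is not the method named for the primary test. A time-averaged longitudinal GEE contrast multiplies the variance by (1 + (T − 1)ρ)/T for T visits with exchangeable correlation ρ. That factor is below 1 whenever T > 1 and ρ < 1. A contrast at one visit has no such factor. Nor can baseline act as a second binary measurement, because every participant enters with ACT ≤19 and so has the same value.

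This is the article's only power statement for the primary outcome. If the 107 relies on a repeated-measures gain, the type II error of the primary test exceeds the 20% that the article implies, and a null result could be over-read as evidence against a 15-point effect.

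**Working it through.** **Inputs from the article.** 107 evaluable per group; 1:1:1 allocation, so the contrast is 107 eUC against 214 app participants; two-sided α = 0.05. The difference is 15%, read here as absolute percentage points. **Assumption.** The eUC rate p0 at 3 months is not given, so it is varied.

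**Can the stated 107 be reproduced?** Not uniquely. Two different sets of inputs both lead to about 107.

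(a) Time-averaged GEE, equal groups, 4 visits, ρ = 0.5, 40% against 55% (visits, correlation and rates all assumed):
n = (1.960 + 0.842)² × [0.40×0.60 + 0.55×0.45] / 0.15² × (1 + 3×0.5)/4
= 7.849 × 0.4875 / 0.0225 × 0.625 = 170.06 × 0.625 = 106.3, rounded up to 107.

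(b) Single-visit two-proportion test, 2:1, 20% against 35%: 106 in the eUC group, with no repeated-measures gain. 63% against 78% also gives 106.

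**Power of the 3-month contrast.** For the pooled two-proportion z test with p1 = p0 + 0.15 and p̄ = (p0 + 2·p1)/3:
SE0 = √[p̄(1 − p̄)(1/107 + 1/214)]
SE1 = √[p0(1 − p0)/107 + p1(1 − p1)/214]
power = Φ[(0.15 − 1.960·SE0)/SE1]

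- p0 = 20%: p̄ = 0.30, SE0 = 0.0543, SE1 = 0.0506, z = 0.863, power 80.6%.
- p0 = 40%: p̄ = 0.50, SE0 = 0.0592, SE1 = 0.0583, z = 0.583, power 72.0%.

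| eUC rate | Power, 107 vs 214 |
|---|---|
| 10% | 91.6% |
| 15% | 85.6% |
| 20% | 80.6% |
| 25% | 76.8% |
| 30% | 74.2% |
| 35% | 72.6% |
| 40% | 72.0% |
| 45% | 72.2% |
| 50% | 73.3% |
| 55% | 75.3% |
| 60% | 78.3% |
| 65% | 82.2% |
| 70% | 87.1% |

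Power is below 80% from about 21% to 62%. At 40% to 45%, where the requirement is largest, 80% power needs about 130 evaluable in the eUC group.

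**Sensitivity to the form of the test.** Simulating the logit Wald test (200,000 runs) gives 80.8%, 74.1%, 72.9% and 73.4% at eUC 20%, 30%, 40% and 50%. The unpooled formula gives 84.3% at 20%, 79.9% at 25% and 73.0% at 40%. The 80% boundary moves by a few points with the formula; the mid-range dip remains.

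**At the number randomised less attrition.** 124 × 0.85 = 105.4. With 105 against 210, power is 79.8% at eUC 20% and 71.2% at 40%. The Abstract gives 432 instead: 144 × 0.85 = 122.4 and 288 × 0.85 = 244.8. With 122 against 245, power is about 86% at 20%, 80% at 30%, 78% at 40% and 79% at 50%.

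**The case against.** The strongest reply is that no shortfall is shown. The eUC rate rests on pilot work that is not reproduced in the article, and 25% to 55% is the reviewer's range. Everyone starts uncontrolled, so a rate of 20% or lower is no less documented, and there the plain 3-month test delivers the stated power. This stands, and it is why the finding is conditional.

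A reader might infer that the 80% belongs to the secondary 3- to 12-month test. The documents do not support that. The power sentence refers back to the 3-month difference, no visit count or correlation is given, and PASS is named beside the GEE macro. The fit with 4 visits and ρ = 0.5 comes from free inputs and uses equal groups, not the 2:1 contrast; a single-visit calculation fits equally well.

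The analysis plan also permits adjustment for baseline values. The binary baseline is constant, but the numeric ACT score is not. A simulation of a baseline-adjusted logistic test (2,500 runs; assumed baseline–outcome correlations 0.3, 0.4 and 0.5) gave 80%, 81% and 84% at eUC 25%, and 74%, 77% and 79% at 40%. So 72% to 77% is an unadjusted figure. Adjustment can recover some power but does not close the gap everywhere, and the power section does not invoke it. Imputation that draws on later visits could likewise recover some.

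Finally, an article may leave input details to the full protocol. That excuses the missing correlation and visit count. It does not excuse attaching an unqualified power figure to a model that differs from the stated primary test.

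**Conclusion.** The mismatch is in the text: a longitudinal binary GEE calculation sizes an outcome that is tested by one 3-month 2:1 contrast. The unqualified claim of 80% or more is therefore not supported for the primary test. Under a 15-point absolute difference, two-sided 5%, 107 against 214 and no adjustment, it holds only if the eUC rate is about 20% or lower, or about 63% or higher. If the rate is 25% to 55%, power is about 72% to 77%, a type II error of about 23% to 28%. At the Abstract's 432 less 15%, the deficit is at most about 2.5 points. It would be wrong to conclude that the trial is underpowered: the eUC rate is unknown and baseline adjustment may help. What is established is that the stated power is not tied to the planned test and fails over a wide middle range of control rates.

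**What to change.** In the Sample Size and Power Calculation section, restate the primary power for the analysis that is planned: the 3-month logit contrast of the combined app groups with eUC at 2:1. Give the authors' own assumed eUC rate, any gain they assume from adjusting for the baseline ACT score, and the power at the number randomised less 15% attrition. If the assumed rate lies between about 21% and 62%, qualify or lower the 80% claim unless a stated adjustment gain makes up the difference. Keep the GEE figure only as power for the secondary average effect over 3 to 12 months.

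The cost is one rerun of the calculation and a rewritten sentence. The stated primary power may become less favourable. Data collection is complete and nothing in it changes; no extra enrolment is needed.

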**Methods:**

Using a 3-arm RCT lasting 12 months, we will assess the effectiveness of PEAKmAAP in reducing morbidity among 432 adolescents (age 12-20 years). The study population includes adolescents with uncontrolled symptoms who receive primary care at the Arkansas Children’s Hospital (ACH) or asthma care at ACH specialty clinics. At baseline, participants are randomly assigned to 1 of 3 groups: (1) PEAKmAAP group, (2) PEAKmAAP-DS group, and (3) eUC group using a smartphone app with daily non–asthma-related notifications. Study procedures will include baseline, 3-month, and 12-month in-person visits and telephone visits at 6 and 9 months. In-person visits will measure the ACT score, lung function, and self-efficacy; telephone visits will measure the ACT score. Participants will complete monthly online surveys to assess health care use and medication use.

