## Methods

### Study Design

The study is a 3-arm RCT with adolescents with uncontrolled asthma (Figure 1). The study will be conducted at the Arkansas Children’s Hospital (ACH), with children receiving asthma care at ACH primary and specialty care clinics. A sample of 370 adolescents (age 12-20 years) and their caregivers will be enrolled. Participants will be randomized 1:1:1 to 1 of 3 groups: (1) a group using PEAKmAAP alone, (2) a group using PEAKmAAP with data sharing (PEAKmAAP-DS), and (3) an eUC group using an app with nonasthma daily reminders. Randomization will be stratified according to 2 strata based on asthma severity status (mild persistent and moderate-to-severe persistent) in order to minimize differences in baseline severity that may potentially bias treatment effects. A 1:1:1 permuted block randomization scheme with varying block sizes will be independently generated by our biostatisticians using nQuery Advisor 7.0 within each stratum to conceal allocation. The randomization list will be kept independent of the research staff to ensure allocation concealment.

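### The article gives three unreconciled sample sizes (432, 370 and 372), and the 372 falls slightly short of its own requirement of 107 per group at 15% attrition

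*Protocol article*

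**What the plan says.** The protocol article states the size of the trial in three places.

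- **Abstract, Methods:** "we will assess the effectiveness of PEAKmAAP in reducing morbidity among 432 adolescents (age 12-20 years").
- **Methods, Study Design:** "A sample of 370 adolescents (age 12-20 years) and their caregivers will be enrolled". The same section sets equal allocation: "Participants will be randomized 1:1:1 to 1 of 3 groups".
- **Methods, Sample Size and Power Calculation:** "we estimated that a sample size of 107 participants in each group will yield at least 80% power to detect the difference mentioned before". The inflation follows: "After adjusting for a 15% attrition rate, the final sample size needed will be 124 in each group (372 total").

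The last section also gives the effect assumed for the primary outcome, an ACT score above 19 at 3 months: the proportion "will be approximately 15% higher in the PEAKmAAP and PEAKmAAP-DS groups compared to the eUC group". The test level is two-sided 5%. The section states neither the proportion expected under enhanced usual care (eUC) nor the within-person correlation used in the GEE calculation.

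The Results section reports that data collection finished in May 2024 and refers to Figure 3 for the numbers screened, enrolled and randomized. That figure was not available for this check.

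**The concern.** A reader uses the planned sample size to judge whether recruitment met its goal and what power the trial was designed to have. Here the same article supports different answers. Measured against 370 or 372, an enrolment of 432 would be an overshoot of about 16%. If 432 was the plan, the same enrolment would simply meet it. The text does not say whether 432 is a plan, a revision or a result, and all three statements are in the future tense.

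The attrition step raises a separate, smaller question. An inflated sample size should leave the required number once the assumed loss has occurred. That means dividing the required number by the fraction retained. Multiplying by one plus the loss rate always gives too little.

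**Working it through.** **Inputs from the article:** 107 required per group; 15% attrition; 124 per group and 372 in total after inflation (Sample Size and Power Calculation); 370 (Study Design); 432 (Abstract); 1:1:1 allocation, hence 2:1 for the two app groups combined against eUC; difference of 15%, read as percentage points; two-sided 5% level.

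**1. Reproducing the stated 124.** 107 × 1.15 = 123.05, rounded up to 124; 3 × 124 = 372. This matches exactly. The article does not state its formula, so the multiplication is inferred from the match.

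**2. The inflation that retains 107.** 107 / (1 − 0.15) = 125.9, rounded up to 126; 3 × 126 = 378. Check: 126 × 0.85 = 107.1.

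**3. What each stated total leaves at 15% attrition, and the attrition it tolerates.** Evaluable per group = (N/3) × 0.85. Tolerated attrition = 1 − 321/N, where 321 = 3 × 107.

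| Stated total N | Per group | Left per group at 15% loss | Attrition at which 107 remain |
|---|---|---|---|
| 370 | 123.3 | 104.8 | 13.2% |
| 372 | 124 | 105.4 | 13.7% |
| 432 | 144 | 122.4 | 25.7% |

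The shortfall below 107 arises for 370 and 372 whatever formula was used. It does not arise for 432.

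**4. Size of the disagreement between totals.** 432 − 372 = 60, and 60/372 = 16%. 372 − 370 = 2, or 0.5%. To reach 432 from 107 per group, attrition would have to be about 25.7%. The only rate stated is 15%.

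**5. What the attrition slip could cost in power.** This needs an assumed eUC proportion p, because none is given. The check used a simple two-proportion test with n in eUC and 2n in the combined app groups, which is not the GEE method named in the article:

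power = Φ{(0.15 − 1.96 × SE₀) / SE₁}

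SE₀ uses the pooled proportion and SE₁ the separate proportions p and p + 0.15.

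Worked at p = 20% (so 35% in the app groups, pooled 30%):
- n = 107: SE₀ = √[0.21 × (1/107 + 1/214)] = 0.0543; SE₁ = √[0.16/107 + 0.2275/214] = 0.0506; power = 80.6%.
- n = 105: SE₀ = 0.0548; SE₁ = 0.0511; power = 79.8%.

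| Assumed eUC proportion | Power, 107 per group | Power, 105 per group | Loss (points) |
|---|---|---|---|
| 5% | 97.4% | 97.2% | 0.2 |
| 10% | 91.6% | 91.1% | 0.5 |
| 20% | 80.6% | 79.8% | 0.8 |
| 40% | 72.0% | 71.2% | 0.8 |
| 60% | 78.3% | 77.5% | 0.8 |
| 70% | 87.1% | 86.5% | 0.6 |

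Over assumed proportions of 5% to 70% the loss is 0.2 to 0.8 points.

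**6. The base of 107.** With the same formula, 80% power needs 106 in eUC at an assumed 20% and between 60 and 130 over the range 5% to 70%. So 107 is compatible with an assumed 20% versus 35%, but the article's inputs neither confirm nor refute it.

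**The case against.** The strongest reply is that 432 need not be a rival target. The Abstract does not call it one, the article appeared after data collection had ended, and Figure 3 may show that 432 is the number enrolled or randomized. This stands as a real possibility. It does not remove the inconsistency, because the Abstract presents 432 as the number who will be studied while Study Design says 370 will be enrolled.

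Several further points also stand:

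- The gap between 370 and 372 may be rounding. That 370 does not divide by three carries no weight, because permuted blocks of varying size within two strata do not guarantee equal arms at any total.
- The attrition slip is two participants per group.
- The Statistical Analysis section keeps all randomized participants in the primary analysis, with multiple imputation if missing at random is reasonable. The 105 completers are therefore not the planned analysis set. The sample size section nevertheless sets 107 as the number needed and adjusts it for attrition, so its arithmetic should hold on its own terms.

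A reader might infer from the 105 that the trial is underpowered. The article does not support that. It says 107 gives at least 80% power, without an exact value, control proportion or correlation, so whether 105 falls below 80% is unknown. A reader might also infer an undisclosed sample-size re-estimation from the 432. Nothing in the text shows one.

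**Conclusion.** The inconsistency holds, at a severity of minor to should-fix. Three totals stand in the current text without explanation. The one that matters is 432 against 370 or 372, a gap of about 60 participants (16%) that no stated input accounts for.

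The attrition error is confirmed but small. At 15% loss, 124 per group leaves about 105, not 107, and this holds without knowing which formula was used. The power loss of under 1 point rests on assumed control proportions, on reading the 15% as percentage points, and on a simple two-proportion formula; it is not a figure the article yields. If 432 is the operative number, there is no shortfall at all. No endpoint, contrast, significance level or analysis method is affected.

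**What to change.** 1. Give one planned enrolment target in the Abstract, Study Design, and Sample Size and Power Calculation.
2. Say what 432 is. If it is achieved enrolment, label it so and keep it apart from the planned number. If it is a revised target, give the calculation and attrition rate behind 144 per group, and state that it replaces 370 and 372.
3. Correct the attrition sentence. Either note that 107/0.85 gives 126 per group, or note that 124 per group delivers about 105 evaluable at 15% attrition and 107 at 13.7%. Do not turn 126 per group (378) into a new enrolment target: data collection is closed, and none of the article's stated totals is 378.

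The cost is wording in three places. No participants, procedures or analyses change. The only loss is that, if 370 or 372 is the planned number, the article can no longer imply that 107 per group remain after 15% attrition.
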